#### 2.6.2. Clinical Effectiveness

Clinical effectiveness outcomes will be assessed as part of the experimental component and collected at varying time points, including (a) Pre-baseline, (b) Primary outcome, and (c) Generalisation measures. These include a combination of clinical self-report and psychophysiological outcomes. *Clinical self-report outcomes* will be collected online via a secure database (REDCap) or, where necessary, administered via telephone interview or postal return, while *Psychophysiological outcomes* will be collected continuously and passively via a smartwatch with data securely transmitted and automatically integrated into a digital health platform accessible to the research team. All self-report and physiological data will be managed in compliance with relevant privacy regulations (e.g., GDPR) and securely stored on password-protected platforms, with de-identification applied for analysis and reporting to ensure participant confidentiality. The full list of outcome measures is presented in Table 3.

**(a)** 
**Pre-baseline measures**

Collected once at enrolment (Week 0), prior to entering the baseline phase. These include socio-demographic characteristics, medical history, and psychosocial profile (e.g., Psychosocial Index [66], Pain Catastrophising Scale [67], and General Self-Efficacy Scale) [68].

**(b)** 
**Primary outcome measures**

Primary outcomes are the target behaviours directly addressed by the intervention. These are assessed daily, throughout the baseline and intervention phases (including at enrolment, Week 0), post-intervention (within 2 weeks of the final session), and at 3- and 6-month follow-ups. They include the following clinical self-report (daily diary) and psychophysiological outcomes of stress regulation, selected for their sensitivity to change and appropriateness for single-case designs.

**
*Clinical self-report outcomes:*
**
*Psychological distress*: Daily ratings of 24 h average distress measured with the 1-item Subjective Units of Distress Scale (SUDS), ranging from 0 (no distress) to 100 (extreme distress) [69], plus ecological momentary assessments every 2 h for 4 days only (2 during baseline and 2 during intervention).*Sleep quality*: Measured each morning using a single-item scale from 0 (worst) to 10 (best), aligned with self-reported wake times to minimise recall bias.
***Psychophysiological outcomes*:** Continuously recorded via a smartwatch using photoplethysmography and an accelerometer. Adherence and data completeness will be monitored via app analytics and automated tracking tools.
*Heart rate variability (HRV) metrics*: Reflects autonomic nervous system (ANS) activity. Higher parasympathetic (vagal) tone indicates improved regulation, whereas low HRV is associated with mental health risk [37,38,39]. HRV Root Mean Square of Successive Differences (HRV-rMSSD) and other time-, frequency-, and nonlinear-domain and composite metrics will be extracted from beat-to-beat intervals, especially during overnight monitoring.*Sleep parameters*: Includes sleep duration, bedtime, sleep onset latency, nocturnal heart rate, wake-up time, and sleep-related temperature deviation (if available).

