**Experimental phases:**

Table 1 and Figure 2 provide a schematic overview of the experimental study design, phases, and timeline. Each single-case experiment, including at least three tiers, begins with a **(i) Baseline phase (usual care)** of 1–3 weeks, with duration randomised for each participant, followed by a **(ii) Intervention phase (WeCare program)** of 6 weeks. A staggered, multiple-baseline design is used: all participants start the baseline at the same time, but the intervention begins at different times (Tiers I–III)—approximately 7 days (end of the 1st week) for Tier I, 11 days (midpoint of the 2nd week) for Tier II, and 15 days (start of the 3 week) for Tier III. This ensures robust within-person controls and reducing external bias. The minimum 7-day baseline allows for the collection of at least five observations, ensuring maximum rigour [59], while accommodating day-to-day variability (e.g., “bad day”) and logistical constraints (e.g., participant availability for an in-person visit). During the Baseline phase, participants will be provided with a *smartwatch* device (Vivoactive 5, Garmin Ltd., Schaffhausen, Switzerland, https://www.garmin.com/en-AU/legal/compliance/, https://www.garmin.com/en-AU/p/1057989/; accessed on 15 October 2025), worn on the wrist for continuous physiological monitoring through the whole study. The device’s display will remain blank, and participants will not have access to any feedback or vital sign data. They will be instructed to continue their daily routines and usual care practices without changes to medication, lifestyle, or activities. To support retention and maintain engagement during the baseline phase, participants will receive one to two brief messages per week acknowledging their data collection and encouraging continued participation. Regular contact of this kind has been shown to improve adherence and reduce attrition in single-case and digital health intervention studies [60].

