At the start of the Intervention phase, participants will receive a *smart ring* device (OuraRing4, Oura Health, Oulu, Finland, https://ouraring.com/terms-of-use, https://ouraring.com; accessed on 15 October 2025), which will serve as their companion device for the *WeCare* program. Unlike the smartwatch, the smart ring allows participants to view their physiological data in real time through an associated app and provides personalised guidance to support behavioural and lifestyle modifications. Each of the above phases will begin with an in-person session that includes participant education, device setup, and usage instructions. Alternatively, this session may be delivered via telehealth or through a pre-recorded video, with the device mailed or couriered to participants. Following the intervention, an optional **(iii) Extension phase** of 2 weeks will be offered, allowing participants to experience the program using the smartwatch as an alternative wearable. This phase will be an integral part of the “acceptability” evaluation conducted during the co-design component and is not intended to test effectiveness. Follow-up assessments will be conducted at 3 and 6 months post-intervention.

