**‘Distal’ generalisation measures**

Assessed at pre-intervention, post-intervention (within 2 weeks of final session), and at 3- and 6-month follow-ups. These aim to assess broader impacts of the intervention on participants’ lives (~15 min per completion) and include measures of general wellbeing, pain interference, social participation, and perceived benefits, etc.

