**Figure 3 sensors-26-00104-f003:**
[figure not shown]
WeCare program: weekly themes, suggested activities, and reflection prompts.

**Table 1 sensors-26-00104-t001:** Detail of experimental phases.

Phase	When It Starts	How Long	Device Used	What Happens
Baseline (Usual care)	*Sample* 1 and 3: 0–2 weeks post-ED care. *Sample* 2: 4–6 weeks post-ED care. *Sample* 4: Any time.	1–3 weeks (7, 11, 15 days by tier)	“Blinded” smartwatch (wrist device)	- In-person onboarding. - Wear smartwatch daily. - Smart ring sized for next phase. - Continue usual care, no changes. - Daily diaries and weekly surveys.
WeCare Program (Intervention)	After baseline phase ends	6 weeks (staggered by tier)	“Blinded” smartwatch Smart ring	- In-person onboarding. - Continue smartwatch monitoring. - Start intervention using a digital health platform and a smart ring as companions to track real-time physiological data and receive personalised education/feedback.
Optional Extension (Device testing)	After intervention phase ends	2 weeks	“Blinded” smartwatch	- Smartwatch (instead of smart ring) as intervention companion. - Test delivery method only. - Part of qualitative, co-design acceptability analysis.

**Table 2 sensors-26-00104-t002:** Participants’ inclusion and exclusion criteria.

Participant Group	Inclusion Criteria	Exclusion Criteria

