All	Aged 18–70 years. Sufficient English proficiency. Willing to wear a smart watch and a smart ring * device for at least 22 hours per day for the next 3 months. * Comfort or infection-control issues related to wearing hand/wrist devices will be monitored and addressed as needed.	History or evidence of substance abuse (e.g., alcohol or illicit drugs) at the time of admission. History of severe mental health disorders, e.g., bipolar disorder or psychoses or chronic depression disorder, determined by medical history or interview. History of unstable or poorly controlled cardiovascular, neurological, or other serious systemic disease that is likely to interfere with study evaluation or participant safety (e.g., uncontrolled blood pressure, unstable arrhythmia, decompensated heart failure, recent myocardial infarction or stroke, and new or uncontrolled metabolic or inflammatory conditions). Evidence of any conditions (e.g., cognitive disorder or dementia) that interfere with the patient’s ability to understand the requirements of the study and their ability to consent. Undergoing, or planning to undergo, surgery or inpatient admission/hospitalisation within the next three months.
Mild-to-moderate injury patient group (*Sample* 1)	Sustained in last 2 weeks a minor-to-moderate injury due to traumatic unintentional cause (e.g., traffic crash, fall, or work-related), such as a whiplash injury, minor fractures, limb fractures, or joint sprains or strains. Presented to RNSH emergency department (ED), Sydney, Australia. Injury Severity Score (ISS) < 15.	Injuries due to assaults or self-harm, because they are often associated with severe additional psychological stress or trauma. Injuries involving the brain. Very minor, localised, superficial soft-tissue injuries, such as small cuts, abrasions, minor bruises, or localised swelling.
Severe injury patient group (*Sample* 2)	Sustained in last 4 weeks a severe traumatic injury due to non-violent cause (e.g., traffic crash, fall, or work-related), such as multi-trauma or severe injuries requiring aggressive therapy and/or admission to the Intensive Care Unit (ICU). Presented to RNSH ED, Sydney, Australia. ISS ≥ 15.	Injuries due to assaults or self-harm. Injuries involving the brain. Very minor, localised, superficial soft-tissue injuries, such as small cuts, abrasions, minor bruises, or localised swelling.

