**(b) PRIMARY OUTCOMES**	OUTCOME	Data collection	Day 0	Daily	Ecological *	Weekly	Pre-program	Post-program	Follow-ups
Mental health status	Subjective Units of Distress Scale	Online/Paper	✓	✓	✓	-	-	✓	✓
Sleep quality	Numeric Rating Scale (0 to 10)	Online/Paper	✓	✓	-	-	-	✓	✓
Autonomic function	HRV metrics	Wearable devices	-	✓ **	-	-	-	✓ **	✓ **
Sleep function	Sleep metrics	Wearable devices	-	✓ **	-	-	-	✓ **^	✓ **^
**(c) GENERALISATION MEASURES**	OUTCOME	Data collection	Day 0	Daily	Ecological *	Weekly	Pre-program	Post-program	Follow-ups
‘Proximal’ Generalisation Measures									
Mental health function	Perceived Stress Scale	Online/Paper	✓	-	-	✓	-	✓	✓
	Patient Health Questionnaire	Online/Paper	✓	-	-	✓	-	✓	✓
	PTSD Checklist for DSM-5	Online/Paper	✓	-	-	✓	-	✓	✓
	Generalised Anxiety Disorder Questionnaire	Online/Paper	✓	-	-	✓	-	✓	✓
Sleep	The Pittsburgh Sleep Quality Index	Online/Paper	✓	-	-	✓	-	✓	✓
Adverse events and life stressors	Self-reported adverse events and stressors diaries	Online/Paper	✓	-	-	✓	-	✓	✓
Consumer perception	Numeric Rating Scale (−7 to +7)	Online/Paper	✓	-	-	✓	-	✓	✓
Quality of life	EQ-5D-5L—Health score (0 to 100)	Online/Paper	✓	-	-	✓	-	✓	✓
Physiological status	HR, RR, Sp02, activity, summary scores, temp	Wearable devices	-	✓ **	-	-	-	✓ **^	✓ **^
‘Distal’ Generalisation Measures									
Mental wellbeing	The World Health Organisation-Five Well-Being Index	Online/Paper	-	-	-	-	✓	✓	✓
Cognitive functioning	Perceived Deficits Questionnaire	Online/Paper	-	-	-	-	✓	✓	✓
Pain interference	Numeric Rating Scales (0 to 10)	Online/Paper	-	-	-	-	✓	✓	✓
Fatigue	Numeric Rating Scales (0 to 10)	Online/Paper	-	-	-	-	✓	✓	✓
Social participation	WHODAS 2.0 Participation Domain	Online/Paper	-	-	-	-	✓	✓	✓
Consumer satisfaction	Was-It-Worth-It Questionnaire	Online/Paper	-	-	-	-	✓	✓	✓
Continuation of use	Three custom questions	Online/Paper	-	-	-	-	-	✓	✓

* Every 2 h for a maximum of 4 days (2 during baseline phase, 2 during intervention phase); ** Continuous monitoring using wearables; ^ If participants are willing to continue the wearable-based self-monitoring past the 11 weeks. ✓ Measured at the specific time point.

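### The post-intervention assessment window coincides with the optional two-week extension, so post-program scores can be taken on or off the program by participant choice

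*Protocol article*

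**What the plan says.** **Timing of the post-program scores.** Section 2.6.2(b) places the primary outcomes, beyond the daily phases, at "post-intervention (within 2 weeks of the final session), and at 3- and 6-month follow-ups". Section 2.6.2(c) gives the proximal measures the same window. The distal measures are "Assessed at pre-intervention, post-intervention (within 2 weeks of final session), and at 3- and 6-month follow-ups".

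**The extension.** Under Experimental phases in Section 2.2.1, the baseline is "followed by a (ii) Intervention phase (WeCare program) of 6 weeks". An optional two-week phase then follows, "allowing participants to experience the program using the smartwatch as an alternative wearable". Section 2.5.3, step 3, describes it as a choice to go on with the intervention on the watch in place of the ring, and Table 1 starts it when the intervention phase ends. Section 2.2.1 adds that it serves the acceptability evaluation and is not a test of effectiveness.

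**The watch.** For the blinded watch, Section 2.2.1 specifies a blank display and states that "participants will not have access to any feedback or vital sign data". The extension row of Table 1 lists the device as a blinded smartwatch and also says "Smartwatch (instead of smart ring) as intervention companion".

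**Follow-up wearable data.** In Table 3, sleep metrics and general physiological status carry the ^ mark at post-program and follow-up. The footnote to that mark reads "If participants are willing to continue the wearable-based self-monitoring past the 11 weeks". HRV has no such mark. Table 2 asks for willingness to wear each "device for at least 22 hours per day for the next 3 months".

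**The concern.** An assessment meant to describe the state after a six-week program can fall on any day of a period in which some participants are still on the program, because they chose to be, and others are not. The protocol neither puts the assessment first nor separates results by extension status. People who opt to continue may well differ from those who stop, for instance in how much benefit they feel, so exposure and self-selection become tied together at that time point. The same imbalance carries into the 3- and 6-month follow-ups, which participants reach after either six or eight program weeks.

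The exposed outcomes are chiefly the distal ones: wellbeing, cognitive functioning, pain interference, fatigue, social participation, satisfaction and intended continuation of use. They have no weekly or daily series, so the post score is their only value between the start of the program and three months. Satisfaction and continuation of use could plausibly respond to being in the extension at the time of asking. With 3 to 8 participants per group, a few continuers can move a group summary.

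The two table entries bear on the same period and on later wearable data. If the extension watch stays blank, it cannot serve as the feedback companion. If its display is on, the instrument that records HRV and sleep becomes part of the intervention while post-program data may be collected.

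**Working it through.** **Inputs.** Baseline 7, 11 or 15 days by tier, nominally up to 3 weeks (Section 2.2.1, Table 1); program 6 weeks = 42 days; extension 2 weeks = 14 days from the end of the program; post window 14 days from the final session; wearable schedule 11 weeks (Table 3 footnote).

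**Reproducing the plan's own figure.** 3 + 6 + 2 = 11 weeks, or 21 + 42 + 14 = 77 days. This matches the footnote, so the 11 weeks include the extension directly after Week 6.

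**Reading 1: the final session is the end of Week 6.** Both the post window and the extension run from day (baseline + 42 + 1) to day (baseline + 42 + 14).

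| Baseline | End of Week 6 | Post window | Extension | Shared days |
|---|---|---|---|---|
| 7 (Tier I) | day 49 | 50–63 | 50–63 | 14 of 14 |
| 11 (Tier II) | day 53 | 54–67 | 54–67 | 14 of 14 |
| 15 (Tier III) | day 57 | 58–71 | 58–71 | 14 of 14 |
| 21 (nominal) | day 63 | 64–77 | 64–77 | 14 of 14 |

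**Reading 2: for those who extend, the final session is the end of the extension.** The windows no longer coincide, but the post score follows 6 + 2 = 8 program weeks for extenders and 6 for the others. Exposure still differs by choice.

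**Which comparisons are touched.** Section 2.8 analyses the primary measures through level and slope change between periods, phase overlap and mixed models. The baseline and intervention data for this end on day 49, 53 or 57, before any extension day. The distal measures have only pre, post and follow-up values (Table 3), so they depend directly on the post window.

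**Follow-up wearables.** Taking 3 and 6 months as about 91 and 182 days after Week 6:
- 3 months: 7 + 42 + 91 = 140 to 15 + 42 + 91 = 148.
- 6 months: 7 + 42 + 182 = 231 to 15 + 42 + 182 = 239.
- The wear commitment in Table 2, counted from enrolment, ends at about day 91.

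Both follow-ups therefore fall outside the commitment in Table 2, for HRV and sleep alike. Section 2.6.2(b) says both are recorded by the same watch, yet only sleep is marked as depending on willingness. The mark also sits on post-program sleep, although under Reading 1 that window ends by day 77, within the 11 weeks.

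**The case against.** The strongest reply is that effectiveness does not rest on the post score. The design is a staggered baseline-versus-intervention comparison within each person, and those data are complete before the extension. A reader might infer from the overlap that the main contrast is compromised; Sections 2.2.1 and 2.8 do not support that. This part of the objection stands in full.

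Second, two weeks is an outer limit. An assessment on the first day after Week 6 would comply and avoid the problem, and a condensed article may leave the order of events inside a window to the full protocol. The protocol also says the extension is for acceptability. This stands in part: compliance is possible but not required, and the purpose of the extension does not keep effectiveness questionnaires out of its two weeks.

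Third, being off the program is not a clean state. Section 2.5.3 lets the last step run on after Week 6 and offers guidance for self-experiments. Team members would also know who extended, so mixing arises only if scores are pooled without regard to that. Both remarks limit the likely size, but the protocol does not say that results will be separated.

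Fourth, a reader might infer that follow-up HRV will come only from volunteers. Table 3 does not say so: HRV carries no ^ mark, Section 2.2.1 has the watch worn throughout the study, and renewed wear at follow-up is not excluded. What the documents show is an inconsistency between two outcomes from one device.

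**Conclusion.** The overlap is in the text. On the natural reading it is complete, 14 of 14 days in every tier; on the other reading, program exposure is 8 versus 6 weeks. The result is a post-program score whose exposure depends on participant choice. It matters mainly for the distal measures and, through unequal program length, for interpreting the 3- and 6-month results. The daily phase comparison is untouched.

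No numerical bias can be attached. The protocol gives neither extension uptake nor any difference between being on and off the program, so a product of the two would only restate what was assumed. The conclusion rests on the timing statements and on the absence of any rule placing the assessment before the extension.

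The blinded label and the Table 3 marks are separate, smaller inconsistencies that need reconciling. Neither is needed to establish the overlap.

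**What to change.** 1. Define the final session as the end of Week 6, and require the post-intervention assessment to be completed before any extension activity starts. This needs no extra visit. The cost is a tighter window, which may lose a few late questionnaires.
2. Record who takes the extension and report the 3- and 6-month results by that status. An earlier post assessment alone does not remove unequal exposure at follow-up. The cost is one recorded item.
3. Reconcile the blinded label in the extension row of Table 1 with the watch's role as intervention companion. If the display is switched on, do not use HRV or sleep data recorded by the watch during the extension as post-program outcome values.
4. Reconcile the ^ marks in Table 3 for HRV and sleep. If wear past the 11 weeks is voluntary, mark HRV too and treat follow-up HRV and sleep as descriptive. If wear is expected of everyone at follow-up, say so and bring the wear period in Table 2 into line.

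Items 3 and 4 are wording corrections. Nothing here changes the sample size or the phase analysis.

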#### 2.5.1. Wearable Integration and Personalised Data-Driven Feedback

The program employs an advance *smart ring* device (OuraRing4, Oura Health, Oulu, Finland, https://ouraring.com/terms-of-use, https://ouraring.com; accessed on 15 October 2025) to provide continuous physiological feedback to participants. Using infrared LEDs, temperature sensors, an accelerometer, and a gyroscope, the ring collects real-time biometric data, including key indicators such as HRV, respiratory rate, sleep metrics, and body temperature.

The associated app applies proprietary algorithms, which incorporate elements of machine learning/artificial intelligence to analyse the data. The app summarises daily and weekly trends, generating health summary scores related to stress, recovery, and activity. Participants will receive daily personalised, data-driven insights based on their individual physiological patterns. These insights, paired with guided reflections and practical suggestions, will support participants’ understanding of their stress and recovery cycles, as well as how their habits influence their health trajectory, encouraging self-awareness and adaptive behaviour.

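### The morning sleep rating, a primary outcome, is made without feedback in baseline but possibly after seeing the ring app's data on the same night in the intervention phase

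*Protocol article*

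**What the plan says.** All references are to the Protocol article.

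- **The ratings (section 2.6.2, Primary outcome measures).** Sleep quality is "Measured each morning using a single-item scale from 0 (worst) to 10 (best), aligned with self-reported wake times to minimise recall bias". Distress is collected as "Daily ratings of 24 h average distress measured with the 1-item Subjective Units of Distress Scale (SUDS", 0–100). Of the primary outcomes the section says: "These are assessed daily, throughout the baseline and intervention phases". The same items therefore supply both sides of the phase contrast.
- **Baseline (section 2.2.1, Experimental phases).** The smartwatch "display will remain blank, and participants will not have access to any feedback or vital sign data".
- **Intervention (section 2.2.1, Experimental phases).** "At the start of the Intervention phase, participants will receive a" smart ring, and "the smart ring allows participants to view their physiological data in real time through an associated app".
- **What the app offers (section 2.5.1).** The ring collects sleep metrics among other signals. The app summarises daily and weekly trends, "generating health summary scores related to stress, recovery, and activity".
- **Use of the data (section 2.5.2, Track).** Participants monitor their data daily and relate it to what they do and how they feel.
- **Passive measures.** HRV and sleep parameters come from the smartwatch, which Table 1 marks as blinded in both phases.
- **Analysis (section 2.8).** Means and trend lines by period, level and slope change, linear mixed-effects models and Tau-U. All compare the intervention phase with baseline.

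**The concern.** The wake-time anchor on the sleep item guards against poor recall. It also places the rating at the moment when the ring's data on that same night may be on the participant's phone. In baseline no such information exists. The conditions under which the item is answered therefore change at the phase boundary, along with the treatment.

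A multiple-baseline design reads a change in level or slope at the start of the intervention as an effect, and trusts it more when it recurs at different start days. A rating shift caused by the display would recur in the same way, because the ring arrives with the intervention in every tier. Neither the randomised start day nor replication across samples can tell the two apart. The stake is the meaning of one primary outcome: an apparent gain could be partly the app's reading repeated back, and a real gain could be masked if the app reads worse than the night felt.

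**Working it through.** **Step 1. Set the conditions side by side.**

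| | Baseline | Intervention |
|---|---|---|
| Sleep item | 0–10, at waking | 0–10, at waking |
| Device data visible to the participant | None | Ring app, real time, including sleep metrics |
| Order of rating and viewing | Not applicable | Not fixed |
| Watch used for passive outcomes | Blinded | Blinded |

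Only the visibility row differs, and it differs from the start of the intervention in all three tiers (after about 7, 11 and 15 baseline days).

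**Step 2. How far a rating could move.** The documents give no figure, so this is an illustration on assumed values. Let the felt quality be 5, the displayed reading be equivalent to D on the same scale, and w the weight the participant gives the display:

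rating = (1 − w) × 5 + w × D

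- D = 7: w = 0.25 gives 3.75 + 1.75 = 5.5; w = 0.5 gives 2.5 + 3.5 = 6.0.
- D = 3: w = 0.25 gives 3.75 + 0.75 = 4.5; w = 0.5 gives 2.5 + 1.5 = 4.0.

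The shift is 0.5 to 1.0 point in either direction, with no change in sleep.

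**Step 3. What a pure rating shift does to one participant's phase comparison.** The plan states no power, effect size or SD, so there is no figure of its own to reproduce. Inputs: n₁ = 7, 11 or 15 baseline days and n₂ = 6 × 7 = 42 intervention days (Table 1); α = 0.05 (section 2.8), taken as two-sided because no side is stated; a constant shift d in within-person day-to-day SDs (assumed); independent days. With Φ the standard normal distribution function,

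P(p < 0.05) ≈ Φ( d × √[1/(1/n₁ + 1/n₂)] − 1.96 )

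The square-root term is √6.00 = 2.449 for 7 days, √8.72 = 2.952 for 11 days and √11.05 = 3.325 for 15 days. At d = 0.5 and 7 days: Φ(1.225 − 1.96) = Φ(−0.735) = 0.231.

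| Assumed shift (SD) | 7 days | 11 days | 15 days |
|---|---|---|---|
| 0 | 5% | 5% | 5% |
| 0.25 | 9% | 11% | 13% |
| 0.5 | 23% | 31% | 38% |
| 0.75 | 45% | 60% | 70% |
| 1.0 | 69% | 84% | 91% |

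Positive autocorrelation lowers these figures. With lag-1 correlation 0.3 the information is multiplied by (1 − 0.3)/(1 + 0.3) = 0.538. At d = 0.5 and 7 days: √(6.00 × 0.538) = 1.797, and Φ(0.899 − 1.96) = Φ(−1.061) = 14%.

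**Step 4. Does pooling help?** Only if the shift varies in sign between people and so averages out. If it is the same for everyone, pooling makes it easier to detect: at 0.25 SD with independent days, 25% for 3 participants and 72% for 12 (15% and 46% with lag-1 correlation 0.3). These pooled figures assume no between-person variation in the shift, which the documents do not establish.

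**The case against.** **Feedback is the intervention.** The Track step asks people to link biometrics with how they feel, and section 2.5.3 aims at better body awareness. A changed appraisal of sleep after seeing one's data is partly intended. This stands, but it does not remove the problem: the rating alone cannot show whether sleep changed or only the number given for it.

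**A safeguard exists.** The watch's sleep parameters and HRV are also primary outcomes and stay blinded, so a self-rated gain with no change on the watch would be visible. This helps in part. Perceived sleep quality and watch-derived sleep measure different things, so disagreement has more than one explanation. The article's remedy for expectation bias, open communication at recruitment and onboarding, does not deal with displayed data.

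**Prompt order is operating detail.** A condensed article may leave it out. But the article does fix the timing of this item and gives the reason, and the chosen timing creates the exposure.

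**Stronger readings that a reader might infer, which the documents do not support:**

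- *That anchoring will produce a shift at each tier's start.* It is a plausible mechanism of unknown size and sign. If the differences between displayed and felt quality vary in direction, the mean shift tends to zero.
- *That the app shows a sleep score.* Section 2.5.1 names scores for stress, recovery and activity; for sleep it names metrics only.
- *That the distress rating is exposed in the same way and can be protected in the same way.* It covers 24 hours, during which scores will already have been seen, and no time of day is given for it. Barring the app until it is submitted could withhold the daily feedback itself.
- *That agreement between self-report and physiology will be inflated in the results.* Section 2.8 names no agreement analysis.

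**Conclusion.** The point holds for the morning sleep rating. It is made without device feedback in baseline, and in the intervention phase at a time when ring data on the same night may be viewable, with no order set. The staggered design cannot separate a display effect on the rating from a change in sleep.

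The size is not known. The 0.5 to 1.0 point example rests on assumed weights and an assumed two-point gap. The single-participant figures (for example 23% to 38% at 0.5 SD, against 5% with no shift) rest on a constant shift and independent days. They show that a moderate shift would matter, not that one will occur.

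For the distress rating the exposure is real but less direct, and it is a limitation to state. The study is an exploratory proof of concept with no power claim, so this does not undermine it. It is an inexpensive improvement, best made before enrolment.

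**What to change.** In section 2.6.2, Primary outcome measures:

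1. Require the morning sleep rating to be submitted before the ring app is opened that day, and send the prompt at the same wake-aligned time in both phases.
2. Add one yes/no diary item asking whether ring data had been seen before answering.
3. Keep all sleep ratings in the primary phase contrast and use the yes/no item only for a sensitivity analysis. Limiting the primary contrast to ratings given before viewing would select intervention days on behaviour that cannot occur in baseline. Days when people check the app first may differ in sleep, stress or engagement.
4. Interpret the self-rating beside the blinded-watch sleep parameters.
5. For the distress rating, keep the prompt at the same time of day in both phases, and state as a limitation that in the intervention phase it is made with app scores already seen. Do not bar app use until it is submitted.

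Cost: app viewing is delayed by a few minutes each morning, and the diary gains one item. The intervention content is unchanged.
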